## Current registration status

Registration of this study started on April 21, 2014, and 110 cases have been
registered. The number of participating facilities has increased to a total of 14, and we are
planning to register the remaining 90 cases within 2 years.

## Discussion

The Agatston score is a coronary artery calcium score that was proposed by Agatston
et al.^10^ in 1990. It has also been
applied for the evaluation of aortic calcification. Since the purpose of this study is to verify
whether vitamin K2 as a drug has an inhibitory effect on calcification, the progression of
abdominal aortic calcification evaluated by the Agatston score will be set as the primary
endpoint.

Few interventional studies examining the inhibitory effect of vitamin K on
calcification have been performed. Brandenburg et al. reported that the aortic valve
calcification volume score progressed by 10% in patients administered with vitamin K1 compared
with 22% in a placebo group, representing a significant vitamin K1-induced attenuation of aortic
valve calcification.^8^ Furthermore, Shea
et al. reported that phylloquinone supplementation slowed the progression of coronary
arterial calcification in healthy older adults.^11^ There have been two ongoing vitamin K interventional studies in dialysis
patients in which vitamin K1 was administered to the interventional group. To date, there has
been no vitamin K2 (menaquinone) interventional trial in dialysis patients. We believe our
present trial will contribute to finding a treatment option for vascular calcification in
dialysis patients.

Vitamin K-related markers are not routinely measured in maintenance dialysis
patients, and the treatment for vitamin K deficiency has not been standardized yet. Therefore,
we believe that not administering vitamin K supplementation for 2 years is not unethical.

The severity of vascular calcification in dialysis patients is higher than that in
healthy subjects. Jansz et al. reported that the degree of coronary calcification was not
significantly different between hemodialysis and peritoneal dialysis patients.^12^ We have assessed that similar treatment effects of
vitamin K can be evaluated in hemodialysis and peritoneal dialysis patients. As patients use
their own peritoneum, deterioration of peritoneal function hinders the continuation of
peritoneal dialysis. Therefore, the time on dialysis is shorter in peritoneal dialysis patients
than in hemodialysis patients. Patients must change the peritoneal dialysis bag by themselves,
and the mean age of the peritoneal dialysis patients is younger than that of hemodialysis
patients. For these reasons, the allocation factors differ between hemodialysis and peritoneal
dialysis.

Although this is an open-trial test, we postulate that physicians will not change
the standard care according to the allocation result because vitamin K administration is
independent of routinely performed CKD-mineral bone disease treatment.

This study has some limitations. First, the long-term effects on cardiovascular
prognosis cannot be evaluated because the observational period is 2 years. Second, instructions
for returning any unused medication and empty medication containers are not included in the
protocol.

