## Treatment details

All patients will first undergo a multi-slice computed tomography (CT) scan of the
abdomen. We will use the Agatston score to quantify calcification. The Agatston score is a
semi-automated tool used to calculate a score based on the extent of arterial calcification
detected by an unenhanced CT scan. The calculation is based on the weighted density score given
to the highest attenuation value (HU) multiplied by the area of the calcification speck (130–199
HU: 1; 200–299 HU: 2; 300–399 HU: 3; and 400+ HU: 4). The calcification of the abdominal aorta
will be measured from the celiac artery branch to the inferior mesenteric artery branch. The
aorta will be regarded as a perfect circle, and only calcifications inside the circle will be
selected. Calcifications of the bifurcating arteries that branch from the abdominal aorta
(celiac, bilateral renal, superior mesenteric, testis, ovarian, and inferior mesenteric
arteries) will be excluded. Dialysis patients will be divided into two groups: a group
administered with vitamin K2 and a control group. The hemodialysis and peritoneal dialysis
patients will be randomly allocated into two groups. Half of the hemodialysis patients and half
of the peritoneal dialysis patients will be administered with vitamin K2 (the vitamin K2
administration group), whereas the other halves will receive the standard care for CKD-mineral
bone disease without vitamin K2 administration (the control group). The following seven factors
will be considered.

Hemodialysis patients: age of 70 years, sex, time on dialysis of 10 years, diabetes,
serum phosphate of 6.1 mg/dL, corrected calcium of 9.3 mg/dL, and a young adult mean
of 70% or a T score of –2.5 in dual-energy X-ray absorptiometry.

Peritoneal dialysis patients: age of 64 years, sex, time on dialysis of 4 years,
diabetes, serum phosphate of 6.1 mg/dL, corrected calcium of 9.3 mg/dL, and a young
adult mean of 70% or a T score of –2.5 in dual-energy X-ray absorptiometry.

The observation period will be 24 months. After performing abdominal CT and
dual-energy X-ray absorptiometry of bone density, an interventional study will be performed. In
the vitamin K2 administration group, menatetrenone (45 mg/day) will be orally administered
in three divided doses. Vitamin K-related biomarkers will be measured before the study and 2,
12, and 24 months later. Other calcification-related biomarkers will be measured before the

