## Justification of sample size

Sample size calculations were based on the studies by Brandenburg
et al.^8^ and Krueger
et al.^9^ Assuming the difference in the
changes in the Agatston score between the two groups was 400 and the standard deviation was 900,
we would need to enroll 80 patients per arm to detect a significant difference with a two-sided
significance level of 5% and a detection power of 80%. Correcting our total sample size of 160
by a dropout rate of 20% resulted in a total sample size of 200.

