## Analysis of the primary endpoint

The primary efficacy end point is the change in abdominal aortic calcification
evaluated by the Agatston score at the 24-month visit versus the baseline visit. While we will
use the change in the abdominal aortic calcification Agatston score after 24 months as an
objective variable, the difference between the vitamin K administration and control group will
be confirmed by covariance analysis. The abdominal aortic calcification Agatston score at the
time of the baseline measurement will be added into the model as a covariate. The significance
level will be set at 5% on both sides. If a Gaussian distribution will not be confirmed in the
residuals, the change in the abdominal aortic calcification Agatston score will be examined
after logarithmic transformation.

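### Allocation is done within dialysis modality, but the stated primary ANCOVA leaves modality out, and the similarity of effects across modalities should be presented as an assumption

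*Protocol article*

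**What the plan says.** **Allocation.** Under Treatment details, the "patients will be randomly allocated into two groups. Half of the hemodialysis patients and half" of the peritoneal dialysis patients receive vitamin K2; the rest receive standard care. Seven factors are considered within each modality. Two of their cut-offs differ: age (70 years for hemodialysis, 64 for peritoneal dialysis) and time on dialysis (10 years and 4 years).

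**Primary model.** Under Analysis of the primary endpoint, the 24-month change is compared between arms by covariance analysis, and the Agatston score at the "time of the baseline measurement will be added into the model as a covariate". No other covariate is named.

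**Sample size.** The assumed difference in the "changes in the Agatston score between the two groups was 400 and the standard deviation was 900". With these, "we would need to enroll 80 patients per arm to detect a significant difference with a two-sided" test, at a "significance level of 5% and a detection power of 80" per cent. Correcting 160 "by a dropout rate of 20% resulted in a total sample size of 200".

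**Reason given for similarity.** The Discussion reports a study in which the degree of coronary calcification was not "significantly different between hemodialysis and peritoneal dialysis patients". The next sentence concludes that similar treatment effects of "vitamin K can be evaluated in hemodialysis and peritoneal dialysis patients". The same paragraph says that peritoneal dialysis patients are younger and have spent less time on dialysis, and gives this as the reason for the different allocation factors.

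**The concern.** There are two linked points, and the first matters more.

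1. **The stated model does not follow the allocation.** Modality is a stratum by design: each arm receives half of each group. Stratified allocation removes chance imbalance in modality from the comparison, but a model without modality still counts the difference between modalities as residual noise. The treatment estimate then varies less than its standard error says. The test is conservative and the confidence interval too wide. How much is lost depends on how far progression differs between modalities. Some difference is plausible, since the Discussion itself says that age and time on dialysis differ.

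2. **The argument for similar effects does not follow.** A non-significant difference does not show equality. The level of calcification is not the effect of a treatment on its progression. The cited comparison concerns the coronary arteries, whereas the endpoint is in the abdominal aorta. No other evidence is offered. If the effects did differ, the pooled estimate would be an average over whatever mix was enrolled, and readers would need estimates by modality to see this.

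**Working it through.** **Inputs from the document (Justification of sample size):** difference 400, SD 900, two-sided 5%, power 80%, 80 per arm, 20% dropout, total 200.

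**Inputs assumed:** the article does not give the split by modality. I take the peritoneal dialysis share f as 10% to 50% of 160 completers, with 1:1 allocation within modality and SD 900. I also assume values for D, the difference in mean progression between modalities.

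**Step 1. The plan's own figure.** n per arm = 2 × (1.960 + 0.842)² × 900² / 400² = 79.5, rounded up to 80. Total 160, and 160 / 0.80 = 200. Power at 80 per arm is 80.3% by the normal approximation and 79.8% by the noncentral t. The stated figures reproduce.

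**Step 2. Cost of leaving modality out.** The standard error of the pooled difference is 900 × √(2/80) = 142.3. If 900 is the residual SD without modality in the model, modality accounts for the fraction R² = f(1 − f)D² / 900² of that variance. The estimate's actual standard error is then 142.3 × √(1 − R²), while the model without modality still reports about 142.3. I take D = 400 (the size of the planned effect) and D = 900 (one SD) as benchmarks:

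| D | f | R² | Actual SE | Reported SE too large by |
|---|---|---|---|---|
| 400 | 10% | 1.8% | 141.0 | 0.9% |
| 400 | 50% | 4.9% | 138.7 | 2.6% |
| 900 | 10% | 9.0% | 135.7 | 4.8% |
| 900 | 50% | 25.0% | 123.2 | 15.5% |

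A simulation with allocation fixed within modality agreed: the reported standard error stayed near 142 in all four cases, and the actual one fell as shown, to within 1 unit. If D = 0 there is nothing to gain, and the added term costs one degree of freedom. The part of D that the baseline score already explains does not count here, so the gain depends on the difference that remains after adjustment for baseline.

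**Step 3. Precision by modality.** With n per arm in the peritoneal dialysis group, the 95% half-width is t × 900 × √(2/n) on 2n − 2 degrees of freedom. For the difference in effect between modalities, the standard error is 900 × √(2/n_PD + 2/n_HD), multiplied by t on 156 degrees of freedom (1.975).

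| Peritoneal share | n per arm, PD / HD | Half-width, PD effect | Half-width, difference between modalities |
|---|---|---|---|
| 10% | 8 / 72 | 2.145 × 450.0 = 965 | 1.975 × 474.3 = 937 |
| 20% | 16 / 64 | 2.042 × 318.2 = 650 | 1.975 × 355.8 = 703 |
| 30% | 24 / 56 | 2.013 × 259.8 = 523 | 1.975 × 310.5 = 613 |
| 50% | 40 / 40 | 1.991 × 201.2 = 401 | 1.975 × 284.6 = 562 |

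Every half-width is at least as large as the planned effect of 400. Power to detect a difference between modalities of 400 is 13% to 29% over the same shares (normal approximation). The trial can describe the effect in each modality but cannot confirm that the effects are alike.

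**The case against.** **The article announces only a pooled comparison.** The aim is stated for dialysis patients as a whole, the design is one two-arm comparison, and the sample size serves that comparison alone. This stands. A reader might infer that the trial assumes its way to a separate conclusion for each modality, but the document announces none.

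**The pooled result is sound even if effects differ.** This also stands. With half of each modality in each arm, modality is not confounded with treatment, and the pooled contrast estimates the average effect over the enrolled mix. A reader might infer that a pooled estimate is invalid, or that the stated power is wrong because an absent effect in peritoneal dialysis would dilute it. With an effect of 400 in hemodialysis and exactly 0 in peritoneal dialysis, the pooled effect would be 360 to 200 and power roughly 71% to 29%. Those figures need an assumed split and the extreme case of no effect in one group, for which the document gives no evidence. The different age and time cut-offs show that the patients differ, not that the drug acts differently.

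**Analyses by modality may be in a plan that is not shown.** This stands too. The article condenses a fuller document, and subgroup tables are commonly left to the analysis plan. They cannot be called missing, so the request for them is a recommendation.

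**The covariate sentence does not say that baseline score is the only covariate.** True, and a fuller plan may add modality. The article does set out the primary model, however, and as set out it does not contain the stratum. It is fair to ask that the stated model match the stated allocation.

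**The sentence in the Discussion only explains why both modalities are enrolled.** That is a fair reading, and it limits the remedy to wording and descriptive reporting. It does not make the inference sound.

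**A modality main effect does not address similarity of effects.** Correct. The two changes serve different purposes: the term brings the standard error into line with the design, and the estimates by modality describe heterogeneity.

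**Conclusion.** The point holds as a minor improvement to the stated analysis. The primary ANCOVA, as described, omits the stratum within which patients are allocated. This leaves the pooled estimate unbiased but makes its standard error too large when progression differs by modality: by about 1% to 3% if mean progression differs by 400 units and about 5% to 15% if it differs by 900. Both differences, and the 10% to 50% peritoneal dialysis share, are assumptions; the document gives neither quantity.

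Secondarily, a non-significant difference in coronary calcification level does not support similar treatment effects, so similarity should be stated as an assumption. What the trial can say about it will be imprecise: about ±401 to ±965 units for peritoneal dialysis alone and ±562 to ±937 for the difference between modalities.

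The documents do not support the view that the pooled comparison is invalid, that the sample size or power is wrong, or that estimates by modality have been ruled out.

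**What to change.** 1. In Analysis of the primary endpoint, add dialysis modality (hemodialysis or peritoneal dialysis) as a factor in the covariance analysis beside the baseline Agatston score. Keep it in the log-transformed analysis if that fallback is used.
2. In the Discussion, say that similar effects in the two modalities are assumed and will be examined, and drop the inference from the coronary comparison.
3. Report the vitamin K2 effect in each modality, and the treatment-by-modality difference, with 95% confidence intervals. Label them descriptive, with no pass/fail test, and limit any statement about one modality to what its interval supports. If the analysis plan already provides for this, a cross-reference is enough.

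**Cost:** one degree of freedom, one small table and a few words. Modality is already known for every patient because allocation uses it. No extra patients, data or significance level are needed. When the article was written, 90 of the 200 patients had still to be registered, so the change could be made well before the 24-month analysis.
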